## **5.2 Investigational products**

The navigation system used for this study is composed of elements of the Aurora Electromagnetic Measurement System from Northern Digital Inc. (Waterloo, Ontario, Canada) and is combined with in-house developed software for the navigation and visualisation. The system is developed for use in the NKI-AvL only, and there is no current intent to commercialize the system. According to Dutch national guidelines (beleidsplan medische apparatuur), and agreements between the METC and the department of clinical physics, a tailored safety management and risk assessment protocol should be followed which is adapted to the specific medical device.

For technical validation of the navigation system before start of the study we will provide:

- A risk assessment, in collaboration with [name] (Clinical physicist)
- A detailed description of the medical device and software, together with a report of pre-clinical tests on system accuracy, in collaboration with [name] (Clinical physicist)
- A report on electrical safety, in collaboration with [name] (Electrical safety officer)
- A safety protocol for sterile use of the probe and reference markers in collaboration with [name] (Sterile safety officer)
- A detailed operating manual for use in the OR, in collaboration with [name] (Teamleader OR)

After all protocols and manuals have been approved, approval of [name] (head of clinical physics department) will allow the use of the navigation system for the study.

The major risk domains for the current study are electrical safety, sterility, and unforeseen inaccuracies leading to misguidance of the surgeon.

The NDI Aurora hardware has been embedded in several commercial navigation systems, such as the Philips Percunav system. Electrical safety is extensively tested and described by NDI, and will be independently validated by [name].

Two components of the system will come in contact with the patient, being the reference patches and the blunt tip probe. The reference patches are developed by Philips in collaboration with NDI, and are provided in a sterile package. The blunt tip probe can withstand autoclave procedures, and will be tested on sterility by [name]. An alternative option is to use a sterile cover which is also used for hand-held ultrasound probes.

Inaccuracies of the system can guide the surgeon into the wrong anatomic direction. This could lead to unwanted disruption of anatomy. In this study, the navigation system will not be used to blindly guide the surgeon, and only visible, approachable regions will be localized and pointed without disruption of anatomy. This minimizes the risks for this study. Furthermore, a quick and reliable safety and accuracy test will be performed before start of surgery. If there are any signs of major inaccuracies, the navigation procedure during surgery will be cancelled. The safety procedure is described at the end of this paragraph.

#### Navigation hardware

The navigation system consists of several components, being 1) the EM field generator; 2) the blunt tip trackable probe; 3) the reference marker-patches; 4) the sensor interface units; 5) the system control unit.

[figure not shown]

Figure 1: Schematic side-view of a typical patient setup for pelvic cancer surgery, combined with the Aurora navigation system

[figure not shown]

Figure 2: Overview of the navigation hardware components and the interconnections between the components

A side-view of the patient setup in combination with the navigation system is shown in figure 1. A schematic overview of the navigation hardware and the interconnections is shown in figure 2. Of the system components, the blunt tip probe and reference patches will come in contact with the patient. Only the blunt tip probe (Fig. 3) will actually be used within the sterile surgical field.

The EM navigation system generates a known electromagnetic field. Small EM sensors which are located within the EM field will generate a current which can be measured through a sensor interface. Based on the current the exact location and orientation of the sensor within the EM field can be determined. The EM sensors are typically 1 mm in diameter and 8-10 mm long. Sensors can easily be embedded in surgical tools, such as a blunt tip probe, a laparoscopic camera, or a surgical knife.

The used EM field generator is a next generation tabletop version. This generator is placed underneath the patient, and has a shielding layer to minimize influence of metal in the table

to the accuracy of the magnetic field. Maier-Hein *et al.* have shown that this EM field generator has an accuracy in the order of 1mm within a clinical environment, which is suitable for our application.

#### *Blunt tip probe*

This is a general purpose digitizing probe with a rigid, straight metal tip (Fig. 3).

Dimensions of the tip: 65 mm long x 3 mm diameter.

The probe will be sterilized via autoclave before every intervention.

[figure not shown]

Figure 3: Aurora standard straight tip 6DOF Probe

#### *Computer with navigation software*

The navigation software is in-house developed. For the study a code freeze will be performed to formalize a software release. In collaboration with the clinical physics department ([name]) the software will be tested on consistency and reliability, and documentation will be stored. The system will be tested in a black-box approach, where an entire chain-test from acquiring CT data with reference markers until the actual navigation to known positions in a phantom will be tested. The software will be installed on a OR-compatible computer with HEPA filters for in-room use.

#### *Safety protocol*

To prevent delays and minimize the impact of the study procedures in clinical practice the following tests will be performed before the start of surgery. When the reference patches have been applied on the patients' skin in the OR, the navigation system is started. Each patch consists of two sensors, resulting in a total of six sensors. The first step is to make a registration between the reference patch positions in the CT scan and the actual positions in the OR according to the navigation system. This is an automatic registration which takes less than one second. The resulting registration is quantified by assessment of the distances between the scanned and actual sensor positions after registration, where distances of 0 cm

are ideal. This is expressed in a root-mean-square (RMS) parameter, which is a general measure for registration accuracy. The distances are also provided for each sensor separately, to be able to localize and solve individual sensor misplacement. Each sensor should have a registration error smaller than 2.0 cm. If this level is exceeded, sensors can be taken out of the registration. A minimum of four remaining sensors should be used in the final registration. The final RMS of the registration should be within 1.0 cm. If this level is exceeded the procedure will be cancelled.

To further validate the system performance, the blunt tip probe will be used to point at each reference sensor. On the navigation screen the tip of the probe should visually be within 0.5 cm of each scanned reference sensor. Finally, as independent check, the probe is used to point at the belly button, which is then visually checked on the navigation system. If discrepancies of over 1.0 cm exist a quick assessment of possible accuracy improvements is done. If discrepancies remain, the navigation procedure during surgery is cancelled.

### **5.3 Use of co-intervention**

No specific restrictions for included patients are specified. Included patients will follow the same pre-operative workup as non-included patients scheduled for a similar operation.

## **6. METHODS**

### **6.1 Main study parameters/endpoints**

During the surgical procedure, iliac vessels and ureters will be identified using the probe. To have an objective measure of accuracy, three locations on the iliac vessel tract will be pointed out by the surgeon without visualization of the navigation system. These points will be the bifurcation of the common iliac artery into the left and right artery, and also both bifurcations into the internal and external iliac artery. The estimated distance of the probe with respect to the bifurcations in the navigation system will be used as accuracy measure. During surgery, the surgeon will search for the ureters and expose them if needed for the surgical procedure. Navigation software and the probe will be used to estimate the tracts of the ureters within the patient. For several tracked positions the actual probe position will be stored in combination with an actual picture of the real situation. The visual measurements in this phase will also be used for assessment of the software usability. Rigid tumours and pathologic lymph nodes along the large vessels will be localized to gain insight in the use of the current navigation system with only external tracking markers. This experience will be used to design a proper clinical study. The addition of an intra-operative XPerCT scan is

---

expected to improve the navigation accuracy. To assess the improvement, we will register the external patches using both the position from the pre-operative CT scan, as well as the position from the XPerCT scan.

### Main endpoint

In this study we aim to evaluate the feasibility and safety of the navigation system by identifying the iliac vessels and ureters.

## **6.2 Randomisation, blinding and treatment allocation**

This is an observational study. All included patients will be subjected to the same procedure, therefore no randomization is required.

## **6.3 Withdrawal of individual subjects**

Subjects can leave the study at any time for any reason if they wish to do so without any consequences. The investigator can decide to withdraw a subject from the study for urgent medical reasons.

If any technical or physical problems occur during the measurement procedure, prohibiting the anticipated measurements, the patient will be withdrawn from the study. This will not affect the scheduled operation.

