### Primary Objective:

Feasibility and safety of an in-house developed electromagnetic navigation system during abdominal surgery.

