### **4.4 Sample size calculation**

This project is a proof of principle study. The goal is to assess feasibility and safety of the electromagnetic navigation system in a clinical environment during surgery. The system is already extensively tested in a non-clinical setting and has shown to be highly accurate. Pre-clinical tests within the OR have shown that some environmental changes might influence the accuracy of the system. However, assessing all combinations of possible environmental changes is impossible. We have to perform this registration study to have an estimate of the expected environmental influences during surgery.

During the course of the study, we have identified an import application for navigation; i.e. locally advanced T3 or T4 rectal tumour and tumour recurrences in the abdomen and pelvic area. Lately, due to logistic reasons (OR planning), the drop-out of patients who signed informed consent was higher than expected. In order to obtain sufficient accuracy measurements to obtain statistical relevant numbers in this study, 20 more patients should be included. This accounts for 15 successful measurements and 30% chance of failure.

---

Inclusion of maximally 95 patients will be sufficient to evaluate and improve the system during abdominal surgery. No sample size calculation is performed.

---

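### Section 6.3 withdraws patients in whom technical problems prevent the measurements, and nothing in the protocol counts them as failures of feasibility, which is the primary objective

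*Protocol*

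**What the plan says.** Section 2 of the protocol gives the primary objective as "Feasibility and safety of an in-house developed electromagnetic navigation system during abdominal surgery". Section 6.1 repeats it as the main endpoint: "In this study we aim to evaluate the feasibility and safety of the navigation system by identifying the iliac vessels and ureters".

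Section 6.3 lists the ways in which a patient leaves the study. Besides the patient's own choice and urgent medical reasons, it adds: "If any technical or physical problems occur during the measurement procedure, prohibiting the anticipated measurements, the patient will be withdrawn from the study". The planned operation goes ahead regardless.

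Three other places bear on the point:

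- Section 4.4 explains the extension. It reports that "the drop-out of patients who signed informed consent was higher than expected", for logistic reasons to do with operating room planning, and concludes that "20 more patients should be included". It adds: "This accounts for 15 successful measurements and 30% chance of failure".
- Section 5.2 (Safety protocol) sets a registration check before surgery. Of the limit on the final root-mean-square error it says: "If this level is exceeded the procedure will be cancelled". How cancelled patients count in the results is not stated.
- Section 8.1 describes landmark distances, a four-level surgeon score for the ureters, usability, and a comparison with pathology. It has no category for a measurement that could not be obtained.

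**The concern.** In a feasibility study, a case in which the equipment fails is an outcome. Section 6.3 handles it as attrition, on the same footing as a patient who changes their mind. Section 4.4 points the same way: it sizes the extension by successful measurements and treats failures as losses to be made up. The distances and scores in section 8.1 exist only for patients who were measured.

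Section 4.4 also says that the study is needed to learn how the operating room environment affects the system. Patients in whom the system fails during surgery may be the most informative on that question, and they are the ones withdrawn.

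At stake is the primary result. If withdrawn patients drop out of the denominator, selection is on the outcome and the feasibility rate is biased upward. A later clinical study planned on that rate would expect too few failures.

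**Working it through.** **The plan's own figure.** Section 4.4 asks for 20 more patients to obtain 15 successes with a 30% chance of failure.

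- 15 × 1.30 = 19.5, rounded up to 20. This reproduces the stated number.
- Dividing by the success probability gives 15 / (1 − 0.30) = 21.4, rounded up to 22. The gap of two patients is small and is not the point here.
- With 20 patients and 30% failure, the expected number of successes is 20 × 0.70 = 14, with 6 failures. These numbers are used below.

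The maximum of 95 has no calculation behind it: "Inclusion of maximally 95 patients will be sufficient to evaluate and improve the system during abdominal surgery. No sample size calculation is performed".

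**Two readings of section 6.3 if all 6 failures are technical.** Feasibility = successes / denominator, with exact (Clopper-Pearson) 95% intervals.

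| Reading | Rate | 95% CI |
|---|---|---|
| Failures stay in the denominator | 14/20 = 70% | 46% to 88% |
| Withdrawn patients left out | 14/14 = 100% | 77% to 100% |

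Under the second reading the rate is 100% whatever the true failure rate, because each failure removes itself from the denominator.

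**If part of the 30% is logistic.** Let t of the 6 losses be technical and 6 − t be drop-outs before the operating room. Among patients brought to the operating room, feasibility is 14 / (14 + t). The completers-only rate is still 14/14 = 100%.

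| t | 14 / (14 + t) | Overstatement by completers-only |
|---|---|---|
| 0 | 14/14 = 100% | 0 points |
| 2 | 14/16 = 87.5% | 12.5 points |
| 3 | 14/17 = 82% | 18 points |
| 4 | 14/18 = 78% | 22 points |
| 6 | 14/20 = 70% | 30 points |

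**If only some technical failures fall under section 6.3.** Suppose that all 6 failures occur in the operating room, that some are cancellations at the section 5.2 check and are counted as failures, and that w are withdrawn under section 6.3. The reported rate is 14 / (20 − w): 14/18 = 78% for w = 2, 14/17 = 82% for w = 3 and 14/16 = 88% for w = 4, against 70% if none is removed.

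**Does another section settle the reading?**

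- Section 9.3 reports numbers included and completed to the ethics committee each year. This shows losses, but the two counts do not separate logistic from technical causes and are not the endpoint.
- Section 6.4 makes technical problems that prevent measurements a reason to end the whole study. It does not say how a single failed case counts.
- Section 8.1 names neither a feasibility proportion nor a failure category.

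None of them counts a withdrawn patient as a failure, and none excludes such a patient from the analysis.

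**The case against.** The strongest reply is that withdrawal from the study is not the same as exclusion from the analysis. Participation ends in the operating room after the measurements anyway (section 5.1), so section 6.3 may mean only that measuring stops. Analysis sets are often left to a statistical analysis plan, which is not at hand. The study is descriptive, with no test or success threshold. This stands in part: a reader might infer that failures are deleted from the data, and the protocol does not say so. But section 6.3 is an explicit protocol rule about the event that shows non-feasibility, and an analysis plan would have to work around it.

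Three further readings are tempting and go too far:

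- *Feasibility is 100% by construction.* This needs a completers-only denominator, which the protocol does not specify. Large distances and ureter scores of dubious or wrong stay in the data.
- *Withdrawn patients leave the safety set.* No safety set is defined, and sections 7.2 and 7.3 record and follow all adverse events without exempting withdrawn patients.
- *The section 5.2 check withdraws patients under section 6.3.* The check takes place before surgery and cancels navigation. Section 6.3 concerns the measurement procedure, which section 5.1 starts once the iliac vessels are visible. Accuracy among patients who pass the check is a legitimate quantity if it is labelled as such.

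The objection to the size also has force. Logistic drop-out is the only cause of loss that section 4.4 names, it does not split the 30%, and it applies that figure to the 20 added patients. Carrying it over to all 95 has no support in the text.

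**Conclusion.** The point holds in a limited form. Section 6.3 withdraws patients for an event that is itself a negative result on the primary objective, and no section counts them as failures. Feasibility can therefore be biased upward, as far as 100% on a completers-only denominator.

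For the 20 added patients the overstatement lies between 0 and 30 points, depending on how many of the 6 expected failures are technical. The upper end assumes that all are technical and all are left out; the lower end, that all are logistic or that withdrawn patients are still counted. These figures illustrate the mechanism and do not predict the result. The firm finding is that the text leaves the handling of failures open on the primary objective. That justifies an amendment, since the cost is very small.

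**What to change.** Replace the sentence in section 6.3 with wording such as: *the patient remains in the study; the measurement is recorded as not obtained, with the reason, and counted as a feasibility failure.* Then state that:

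- the feasibility denominator is all patients brought to the operating room for navigation;
- cancellations at the section 5.2 check count as not feasible, with the check itself unchanged;
- logistic drop-outs before the operating room are reported separately;
- landmark accuracy is conditional on passing the check;
- every patient who had any study procedure, including the extra CT, stays in the safety denominator. This is a clarification, since the protocol does not say that they leave it.

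The cost is a short amendment and one reason-for-failure field on the case report form. No patients or procedures are added. The reported feasibility will look less favourable.

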## **6.4 Premature termination of the study**

Reasons for premature termination of the study are:

- Occurrence of any serious adverse events that can in anyway be related to the study.
- Technical problems that prevent measurements to be performed.

## **6.5 Monitoring and auditing**

There will be no planned monitoring or auditing visits scheduled.

---

## **7. SAFETY REPORTING**

### **7.1 Section 10 WMO event**

In accordance to section 10, subsection 1, of the WMO, the investigator will inform the subjects and the reviewing accredited METC if anything occurs, on the basis of which it appears that the disadvantages of participation may be significantly greater than was foreseen in the research proposal. In this case the study will be suspended pending further review by the accredited METC.

### **7.2 Adverse and serious adverse events**

Based on the minimal extent of the planned intervention, no SAE's are expected for this study.

Adverse events, AE, are defined as any untoward medical occurrence, unintended disease or injury, or untoward clinical signs (including abnormal laboratory findings) in subjects, users or other persons, whether or not related to the investigational medical device.

All adverse events reported spontaneously by the subject or observed by the investigator or his staff will be recorded.

A serious adverse event, SAE, is an adverse event that:

- a) led to death,
- b) led to serious deterioration in the health of the subject, that either resulted in
  - 1) a life-threatening illness or injury, or
  - 2) a permanent impairment of a body structure or a body function, or
  - 3) in-patient or prolonged hospitalization, or
  - 4) medical or surgical intervention to prevent life-threatening illness or injury or permanent impairment to a body structure or a body function,
- c) led to fetal distress, fetal death or a congenital abnormality or birth defect

All SAEs will be reported through the web portal *ToetsingOnline* to the accredited METC that approved the protocol, within 15 days after the investigator has first knowledge of the serious adverse reactions.

SAEs that result in death or are life threatening should be reported expedited to the METC. The expedited reporting will occur not later than 7 days after the responsible investigator has first knowledge of the adverse reaction. This is for a preliminary report with another 8 days for completion of the report.

---

If serious adverse effects come up that are related or can in any way be related to the study, the study will terminate.

### **7.3 Follow up of adverse and serious adverse events**

All adverse events will be followed up until they have abated, or until a stable situation has been reached. Depending on the event, follow up may require additional tests or medical procedures as indicated, and/or referral to the general physician or a medical specialist.

### **7.4 Data Safety monitoring board (DSMB)**

Not applicable.

---

## **8. STATISTICAL ANALYSIS**

### **8.1 Descriptive statistics**

In this registration study, distances will be measured between the estimated probe positions with respect to the bifurcation of the common iliac artery into the left and right artery, both bifurcations into the internal and external iliac artery and ureters. Measurements will be compared within patients to assess patient specific systematic errors, and between patients to assess system specific systematic errors. Due to the nature of a registration study, significance can not be estimated. However, usability and subjective assessment of experience by the surgeons will be valuable for future projects. Assessment of the ureter tracts will be based on the surgeon's opinion, and scored in terms of excellent, reasonable, dubious or wrong. Actual assessment of tumour boundaries and suspected lymph node locations will be recorded and cross-referenced with pathology

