#### Actual measurements:

- First the surgeon will point the blunt tip probe at the bifurcation of the aorta into the left and right common iliac artery, and also both bifurcations into the internal and external iliac artery. These measurements will be performed without direct

visualization of the navigation system to the surgeon. For each pointed position the estimated position on the navigation system will be stored.

- In the second part, the surgeon will use the navigation system and the probe to localize the ureters. These are generally not visible for the surgeon. The resulting location of ureter tracts will be visually assessed by the surgeon in terms of trueness.

Total time of the proposed preparation and measurements during the surgical procedure will take no longer than 20 minutes. Extra time needed to use the navigation system during surgery will be recorded.

Specific participation for the patient in the study ends during the operation after the measurements have been performed.

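### Distances from probe to landmark carry no direction, so comparing them cannot tell a system-wide offset from equal-sized patient-specific offsets, as section 8.1 intends

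*Protocol*

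**What the plan says.** Section 6.1 of the protocol has the surgeon point at landmarks blind to the screen: "three locations on the iliac vessel tract will be pointed out by the surgeon without visualization of the navigation system". It then fixes the outcome: "The estimated distance of the probe with respect to the bifurcations in the navigation system will be used as accuracy measure".

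Section 8.1 repeats that choice, saying that "distances will be measured between the estimated probe positions with respect to the bifurcation of the common iliac artery", with the two internal/external iliac bifurcations and the ureters added. The next sentence gives the purpose: "Measurements will be compared within patients to assess patient specific systematic errors, and between patients to assess system specific systematic errors".

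Section 8.1 plans no inference: "Due to the nature of a registration study, significance can not be estimated". Section 4.4 has no sample size calculation.

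The raw data go further than the analysis variable. Under the actual measurements in section 5.1, "For each pointed position the estimated position on the navigation system will be stored". The preparation steps of the same section provide a CT segmentation of the iliac vessels. No section names a signed, per-axis or vector error.

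**The concern.** A systematic error in a navigation system is an offset with a size and a direction. If it is the same in every patient, it belongs to the system. If it differs between patients, for example because each registration is shifted differently, it belongs to the patient. The two are told apart by whether the error vectors point the same way, and a distance discards exactly that.

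The variable and the purpose given in section 8.1 therefore do not fit each other. Accuracy is a secondary objective, and the protocol makes further studies depend on the system proving safe and accurate. A reproducible system offset can in principle be calibrated out. Offsets that vary in direction from patient to patient, or random tracking error, cannot be removed that way. An analysis confined to distances may leave the team unable to say which of these it has, and cannot tell it in which direction to correct.

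**Working it through.** The protocol gives no accuracy figure, error SD or offset for this analysis, so there is no stated figure to reproduce. The number of landmarks, three, is from section 6.1. All offsets and SDs below are assumptions for illustration.

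**Model.** Error at a landmark = offset vector + random error, the latter normal with SD σ on each of three axes. Distance = length of the error vector. With offset length μ:

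- mean distance = σ√(2/π)·exp(−μ²/2σ²) + (μ + σ²/μ)·erf(μ/(σ√2)); for μ = 0 it is 2σ√(2/π) = 1.596σ
- SD of distance = √(μ² + 3σ² − mean²)

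Both formulas contain only the length μ. The direction of the offset drops out.

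**Step 1: system-wide against patient-specific offset.** Case A: every patient has the same 8 mm offset. Case B: each patient has an 8 mm offset in a random direction. In both, σ = 4 mm.

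- Mean: 4 × 0.798 × exp(−2) + (8 + 2) × erf(1.414) = 0.43 + 9.55 = 9.98 mm
- SD: √(64 + 48 − 9.98²) = 3.53 mm

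A simulation of 200,000 patients with three landmarks each gave:

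| Summary (mm) | A: shared offset | B: patient offsets |
|---|---|---|
| Mean distance | 9.98 | 9.98 |
| Overall SD of distance | 3.53 | 3.53 |
| SD of patient mean distances | 2.04 | 2.04 |
| Within-patient SD of distance | 3.53 | 3.53 |
| Length of overall mean error vector | 8.00 | 0.02 |

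The SD of patient means is simply 3.53/√3 = 2.04. The distances show no clustering by patient in either case, although in B every patient has an 8 mm offset of their own. Since only μ enters the formulas, A and B agree for any offset size as long as the random error is isotropic.

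With only 15 patients, the number of further successful measurements sought in section 4.4, the mean vector has average length 8.04 mm in A and 2.14 mm in B (the latter is sampling noise). The separation survives a small sample.

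**Step 2: offset against random error.** With no offset and σ = 3 mm, mean distance = 1.596 × 3 = 4.8 mm. A mean distance well above zero is thus no evidence of systematic error. Two further cases have nearly the same mean:

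- no offset, σ = 4: mean 6.38 mm, SD of distance 2.69 mm
- offset 5.58 mm, σ = 2: mean 6.30 mm, SD of distance 1.87 mm

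The means barely differ but the spreads do, so distances retain some information here.

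**Step 3: patient offsets of varying size.** If patient offsets vary in size as well as direction, a badly shifted patient has three large distances together. Simulated intraclass correlation of distances: 0.00 with no patient offset; 0.24 with offset SD 3 and random SD 3 mm per axis; 0.62 with offset SD 4 and random SD 2 mm per axis.

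**The case against.** The strongest objection is that the protocol never says unsigned or Euclidean. Positions are stored, the aim of 8.1 is sound, and whether error is handled per axis or as a magnitude could be left to an SAP that is not shown. The first part stands as far as it goes: unsigned is inferred from the ordinary meaning of distance, and data capture is not at fault. But the protocol itself states both the variable and its purpose, and the two do not match. That is more than a missing detail.

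A reader might infer that a correctable offset and pure noise would look identical in the distances. They would not. In the 6.3 mm example of step 2 the SDs of distance differ, and with 15 patients and three points each the sample SD ranks the two cases correctly in about 99% of simulated replicates. That relies on isotropic normal error, and it gives no direction. Likewise, it is too strong to say that within-patient comparison of distances shows nothing about patient offsets: step 3 shows clustering when offset sizes vary.

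A reader might also infer that the three points per patient will be treated as independent, giving standard errors that are too small. Section 8.1 is descriptive, plans no interval or test, and does not say this.

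Nor does section 6.1 say that the pre-operative CT and XPerCT registrations will be compared by fit at the patches. It says only that the patches will be registered both ways to assess the improvement.

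Finally, registration error includes rotation, which moves the three landmarks differently. A simple vector model would put that into its residual. This is fair, and the fix allows for it.

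**Conclusion.** The point holds in a limited form. As written, comparing distances cannot separate a system-wide offset from equal-sized patient offsets of differing direction, and cannot give the direction of any offset. In the illustration every distance summary agrees while the mean vectors are 8.00 and 0.02 mm. The millimetre values are assumed; the equality of the distance summaries needs only isotropic random error and offsets of equal size. On offset against random error the limitation is partial: the mean confounds them, and spread and clustering help only under a model.

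This should be corrected before analysis. It concerns a secondary objective in a descriptive study, and nothing is lost in data collection.

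**What to change.** In section 8.1, state that for each landmark the signed error components (left-right, antero-posterior, cranio-caudal, in a common patient frame) will be computed from the stored probe positions and the landmark positions in the CT reconstruction. Then report:

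- the mean error vector over patients, overall and per landmark, as the system-specific error;
- the between-patient spread of the patient mean vectors as the patient-specific error, noting that with three landmarks this spread also contains some residual error;
- the remaining within-patient spread as residual error, stating that it includes rotation effects.

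Keep distance, as in section 6.1, as a descriptive summary of overall accuracy.

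The cost is a change of wording and slightly more analysis work. No new data, procedures or patients are needed.
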